### Statistical analysis

Baseline demographic and clinical characteristics will be presented in both groups. Quantitative variables will be defined by mean and standard deviation. Continuous variables will be compared using Student’s *t*-test (normal distribution) or Mann–Whitney test (non-normal distribution). Qualitative variables will be defined by frequency and compared using the chi-squared test or Fisher’s exact test. The proportion of patients that meet the primary outcome will be calculated in the control group and the intervention group. The primary endpoint will be analysed using the chi-squared test comparing the unadjusted risk ratios in each arm. The estimates of risk ratios will be adjusted with multivariate analysis by logistic regression. Adjustment will be performed for age, gender, and history of diabetes, hypertension, or obesity which are the most important factors related to the mortality and disease progression in patients with COVID-19 [27]. Study site will also be included in the multivariate analysis. As a secondary analysis, survival analysis to show the effect of dexamethasone on the primary endpoint in each arm will be performed using Kaplan–Meier curves and log-rank test. A *p*-value of less than 0.05 will be considered statistically significant. Statistical analysis will be performed with the SPSS V28.0 software (SPSS, Inc. Chicago, IL, USA). CONSORT reporting guidelines will be followed to ensure that results are presented in a complete, detailed, and systematic way.

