### Intervention

Patients in the intervention group will receive an intravenous dose of 6 mg once daily from day 1 to day 3, followed by an oral dose of 6 mg once daily from day 4 to day 7 (Fig. 1). For participants unable to take an oral drug, intravenous dexamethasone will be given. We selected the same dose as the RECOVERY trial. Participants randomized to the control group will receive a standard of care. Given that pulmonary disease can progress rapidly in patients with COVID-19, patients will be closely monitored. For improving intervention adherence, a real-time medication monitoring system will offer monitoring of participants’ medication control combined with a short message service (SMS) after discharge. Study participants will receive the best standard of care according to the current COVID-19 Treatment Guidelines. Hospitalized patients who do not require supplemental oxygen can receive anticoagulants for the prevention of venous thromboembolic disease, gastric ulcer prophylaxis, hydration, antipyretics, antibiotics, and bronchodilators. Corticosteroids in patients requiring oxygen support in the control group will be received. In addition, remdesivir, tocilizumab, baricitinib, tofacitinib, and sarilumab will be considered in case of a worsening of disease status [13]. All chronic medication prescribed to the patient is permitted to continue at the discretion of the responsible physician/investigator.

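### As the analysis rule is written, an in-hospital death would count in length of stay like a live discharge on the same day: a small bias that can point the wrong way in a secondary outcome

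*Protocol article*

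**What the plan says.** The Secondary outcomes section lists hospital length of stay by name only, with no start point and no rule for patients who die in hospital. The other listed outcomes (the ARDS-or-death composite, need for ventilation, 90-day mortality, readmission, adverse events) are all events, so length of stay is the only continuous one.

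The Statistical analysis section gives one general rule for such variables. On summaries: "Quantitative variables will be defined by mean and standard deviation". On testing: "Continuous variables will be compared using" Student's t-test if normally distributed, otherwise the Mann–Whitney test. Time-to-event methods appear once, as a secondary "survival analysis to show the effect of dexamethasone on the primary endpoint in each arm". No stated method lets death enter the analysis of stay as anything other than the end of the stay.

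For interpretation, the Intervention section schedules the first three days of dexamethasone by vein ("intravenous dose of 6 mg once daily from day 1 to day 3") and the remaining four days of the course by mouth. The control arm has no scheduled study doses: "Participants randomized to the control group will receive a standard of care". The Discussion acknowledges that the trial is not blinded.

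**The concern.** Death ends a hospital stay. If stay is compared as a plain number, a death on day 10 equals a discharge on day 10 and looks better than survival with discharge on day 25. The trial's hypothesis is that dexamethasone reduces ARDS and death. If that is true, some patients who would have died early become survivors with long stays, and the treated arm can look worse on stay because it did better on survival. If the drug were harmful, the same mechanism could flatter it. What is at stake is the direction of one secondary conclusion; the primary analysis is not affected.

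**Working it through.** **What the article supplies.** 126 patients per group and a t-test or Mann–Whitney rule. It states no figure for length of stay, so there is nothing to reproduce. It gives no mortality rate, distribution of stay or time of death. Every such input below is an assumption, varied over a range.

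**Simple arithmetic.** Suppose treatment turns a fraction d of patients from in-hospital deaths into survivors and changes nothing else. The mean raw stay in that arm then changes by

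d × (stay if saved − stay until death).

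Example: d = 5%, death on day 10, discharge on day 25 if saved. The change is 0.05 × (25 − 10) = 0.75 day longer, although outcomes improved. The sign depends on saved patients staying longer than they would have lived in hospital. If deaths came after very long stays, the shift would shrink or reverse.

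**Simulation.** 126 per arm, 1,000 trials per scenario. Assumed: median stay 7 days, saved patients staying about 20 days, deaths around day 6 or day 15, mortality cut by about one third, no other effect on stay. The arithmetic column uses the medians (20 − 6 = 14 or 20 − 15 = 5). The simulated early-death means are a little higher because stays are skewed.

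| Mortality, control → dexamethasone | Death around day | Arithmetic (days) | Simulated difference in mean (days) | Mann–Whitney rejection, raw stay | Rejection, deaths ranked last |
|---|---|---|---|---|---|
| 3% → 2% | 6 | 0.010 × 14 = 0.14 | 0.17 | 7.3% | 6.1% |
| 3% → 2% | 15 | 0.010 × 5 = 0.05 | 0.05 | 5.1% | 5.5% |
| 5% → 3.3% | 6 | 0.017 × 14 = 0.24 | 0.28 | 6.7% | 4.8% |
| 5% → 3.3% | 15 | 0.017 × 5 = 0.09 | 0.10 | 4.1% | 4.1% |
| 10% → 6.7% | 6 | 0.033 × 14 = 0.46 | 0.49 | 7.9% | 5.9% |
| 10% → 6.7% | 15 | 0.033 × 5 = 0.17 | 0.17 | 5.2% | 5.8% |
| 15% → 10% | 6 | 0.050 × 14 = 0.70 | 0.79 | 12.5% | 4.9% |
| 15% → 10% | 15 | 0.050 × 5 = 0.25 | 0.25 | 5.8% | 6.3% |

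The Monte Carlo standard error of a rejection rate near 5% is √(0.05 × 0.95 / 1000) = 0.7 percentage points.

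**Direction on the rank scale.** Let P be the probability that a treated patient's stay exceeds a control's. On raw stay with early deaths, P − 0.5 runs from +0.006 to +0.028, against the better arm. With later deaths it is close to zero (−0.001 to +0.004). Ranking deaths last gives 0.000 to −0.006 across all scenarios, so the shift disappears or slightly favours the arm with fewer deaths.

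A real shortening of stay from preventing ARDS is left out. It would add to these figures with the opposite sign.

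**The case against.** The strongest reply is that the article never assigns a test to length of stay by name. The general rule follows the sentence on baseline characteristics, and the handling of deaths may sit in the full protocol or a statistical analysis plan that is not shown. That stands in part: a reader might infer that the article says deaths will be treated as discharges, and it does not. But the article does state a method. Stay is the only listed outcome that method fits, and time-to-event methods are limited to the primary endpoint. Applied as written, the rule has this consequence.

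A second reply is that mortality is reported alongside, in the primary composite and as a 90-day outcome. That limits the risk of misreading but does not correct the comparison. It does mean that calling the stay result uninterpretable would go too far, as do the modest sizes above.

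A reader might also infer that intravenous dosing on days 1–3 builds a three-day minimum stay into one arm. The documents do not support this. They schedule a route, set no minimum stay and do not tie discharge to completing those doses. Both arms enrol only patients who need hospital care, and the daily assessments and the chest X-rays on days 1, 4 and 7 apply to both. In the same kind of simulation, with equal mortality of 3%, imposing a three-day floor on the treated arm added about 0.2 day at a median stay of 3 days (Mann–Whitney rejection 30%), 0.08 day at 4 days and 0.01–0.02 day at 5 days or more. If the route does prolong stay, that is a real consequence of the assigned strategy. What remains is a note for interpretation: the schedule exists in one arm only of an open-label trial and may delay discharge.

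**Conclusion.** The point holds as a minor, directional weakness in a secondary outcome. Under the stated rule, in-hospital death and live discharge on the same day are indistinguishable, and an arm with fewer deaths can appear to have longer stays. Under the assumed values the mean is distorted by about 0.05 to 0.8 day. The Mann–Whitney test is nearly unaffected when deaths come late, rejects in 4–8% of trials for control mortality up to 10%, and reaches 12.5% only at 15% mortality with early deaths. These sizes rest wholly on assumed mortality, timing of death and stay. Only the mechanism follows from the article itself.

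**What to change.** State in the analysis section that length of stay will be compared as time from randomisation to live discharge, with in-hospital death as a competing event, in all randomised patients. Present cumulative incidence curves of live discharge by arm. A simpler alternative keeps the Mann–Whitney test but ranks in-hospital deaths as the worst outcome. Report raw stay descriptively by vital status.

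Do not add a landmark analysis starting at day 3. It would condition on remaining in hospital, a post-randomisation event that may differ by arm. At most, say when interpreting stay that intravenous dosing on days 1–3 is scheduled in one arm only and that discharge decisions are unblinded.

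The cost is small: a change of analysis wording and a summary slightly less familiar to readers. Discharge and death dates must be recorded for every patient. The article does not list them as data items, though computing stay and the planned Kaplan–Meier analysis already call for most of them. No visit or treatment changes.

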### Randomization

Eligible, consenting patients will be randomly assigned in a 1:1 ratio to receive either dexamethasone plus standard of care (intervention group) or standard of care alone (control group). Randomization will be done within the REDCap system with unpredictability of assignments. Our statistician created a randomization schedule using a permuted block design, so equal numbers are assigned to each group. This system ensures a balanced allocation of subjects to the study arms. Records of individual assignments to each group will be de-identified (user number and centre ID instead of patients’ names), sequentially numbered, and stored on a secure computer system. Local investigators in participating centres are the only authorized personnel to interact with the radomization system through a username and password. Once eligibility is confirmed in the electronic case report form, the treatment group is assigned by the system. Dexamethasone will be provided free of charge for this study by the organization funding. According to the ethical principles for medical research of the Declaration of Helsinki, the use of no placebo (no intervention) is acceptable when no proven intervention exists. The Spanish Agency of Drugs and Medical Devices and the Ethics Committees did not mandate a blinded design or the administration of a placebo.

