### Sample size

We powered the study to assess whether the intervention would reduce the incidence of ARDS. Based on available evidence, we estimate a 30% risk of ARDS in the control group [2]. We are looking for an ARDS 10% absolute reduction in the intervention group. Assuming 80% power and two-sided alpha = 0.05, 226 participants would be needed to detect the resulting reduction of ARDS from 30% in the control group to 20% in the intervention group. We adopted a sample size of 252 (126 per group) to compensate for the potential loss to follow-up of some participants.

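### The adjusted risk ratio is to come from a logistic model, which estimates an odds ratio; no step to obtain a risk ratio is stated

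*Protocol article*

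**What the plan says.** The Statistical analysis section of the protocol article first fixes an unadjusted analysis of the binary 30-day composite: "The primary endpoint will be analysed using the chi-squared test comparing the unadjusted risk ratios in each arm". It then turns to adjustment: "The estimates of risk ratios will be adjusted with multivariate analysis by logistic regression". The listed covariates are age, sex, history of diabetes, hypertension or obesity, and study site. The section does not mention an odds ratio. Nor does it mention standardised predictions, a log-binomial model or a Poisson model.

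The expected event rates are in the Sample size section: "we estimate a 30% risk of ARDS in the control group", with a target "reduction of ARDS from 30% in the control group to 20% in the intervention group". These rates are for ARDS alone. The primary outcome also counts deaths from any cause.

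**The concern.** The adjustment sentence names a measure and a model that do not match. Exponentiating a logistic treatment coefficient gives an odds ratio conditional on the covariates. When events are rare this is close to the risk ratio, but at 20% to 30% it is not. An analyst who follows the sentence literally would have an odds ratio under a risk-ratio label.

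The adjusted estimate for the primary endpoint, and its comparison with the unadjusted one, are at stake. Printed side by side, the two figures would seem to show that adjustment strengthened the effect, when much or all of the difference could come from the change of scale.

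**Working it through.** **Plan's own figures.** The document gives no risk ratio or odds ratio to reproduce. It gives the two rates and their difference: 30% − 20% = 10 percentage points, as stated. The sample size total does not enter this point.

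**Inputs (Sample size section).** Control risk p0 = 0.30; intervention risk p1 = 0.20.

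**Step 1: the two measures.**
- Risk ratio: RR = p1/p0 = 0.20/0.30 = 0.667, a relative reduction of 33.3%.
- Odds ratio: OR = [p1/(1 − p1)] / [p0/(1 − p0)] = (0.20/0.80)/(0.30/0.70) = 0.2500/0.4286 = 0.583, which read as a risk ratio is a reduction of 41.7%.
- Link between them: OR = RR × (1 − p0)/(1 − p1) = 0.667 × 0.70/0.80 = 0.583.

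**Step 2: size of the misreading.**
- Relative reduction: 41.7% − 33.3% = 8.3 percentage points too large (before rounding).
- Implied intervention risk: 0.583 × 30% = 17.5%, an absolute reduction of 12.5 points instead of 10.
- Log scale: ln(0.583)/ln(0.667) = 1.33, so the odds ratio lies a third further from no effect.

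**Step 3: the opposite direction.** With the two rates exchanged (20% control, 30% intervention), RR = 0.30/0.20 = 1.50 and OR = 0.4286/0.2500 = 1.71. The exaggeration is away from 1, whichever arm does better.

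**Step 4: other rates (assumed, to show the range).**

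| Control | Intervention | RR | OR |
|---|---|---|---|
| 30% | 25% | 0.833 | 0.778 |
| 30% | 15% | 0.500 | 0.412 |
| 20% | 13.3% | 0.667 | 0.615 |
| 40% | 26.7% | 0.667 | 0.545 |

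The composite includes every ARDS event, so its rate in each arm is at least the ARDS rate. At the same risk ratio, the last two rows show the gap growing as the control rate rises.

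**Step 5: effect of adjustment (covariate strength assumed).** The odds ratio is non-collapsible: adding a prognostic covariate moves it further from 1 even without confounding. With one normal covariate and the average risks held at 30% and 20%:
- log-odds 0 per SD: conditional OR 0.583;
- log-odds 0.5 per SD: conditional OR 0.569;
- log-odds 1.0 per SD: conditional OR 0.532.

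The risk ratio is 0.667 in all three cases. The direction is general; the amounts depend on the assumed strength.

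**Step 6: do the remedies recover the risk ratio?** In a simulation of 400,000 patients under the same three settings, standardised logistic predictions and a Poisson log-link model each gave 0.668 to 0.673, against a true 0.667.

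**The case against.** The best defence is that a logistic model can yield a risk ratio: predict each patient's risk under both arms, average, and take the ratio. On that reading the sentence is incomplete, not wrong, and a condensed article may leave the step to a fuller document that is not shown. This stands in part. It means that misreporting is possible, not certain. It does not clear the sentence, which itself fixes both the measure and the model and gives nothing to connect them; the natural reading is that the coefficient is used directly.

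The text also does not support several stronger readings that a reader might infer:
- **That the primary result is compromised.** The section assigns the primary endpoint to the chi-squared test and unadjusted risk ratios, and neither depends on the logistic model.
- **That significance testing is biased.** With no treatment effect, the odds ratio and the risk ratio are both 1, so the scale mismatch does not create a false signal.
- **That the plan favours dexamethasone.** Step 3 shows that harm would be exaggerated as well.
- **That the adjusted estimate will be inflated by a known further amount.** The document gives no covariate strengths, so the figures in Step 5 are illustrations.
- **That placing risk ratios within each arm is a second error.** A risk ratio is between arms, but the preceding sentence calculates proportions in both groups, so the intended comparison is clear. This is wording only.

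**Conclusion.** The point holds as a mismatch between measure and model in the adjusted analysis, of moderate importance. At the protocol's own ARDS rates, an exponentiated logistic coefficient presented as a risk ratio would be about 0.58 where the risk ratio is 0.67, before any further shift from the covariates.

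This rests on two conditions. The coefficient must be reported under the risk-ratio label, which the document neither states nor rules out. The composite must also occur at rates near or above those assumed for ARDS, with a similar risk ratio.

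**What to change.** Replace the adjustment sentence with one that names a matching pair. Any of these will do:
- an adjusted risk ratio from modified Poisson regression with robust standard errors;
- an adjusted risk ratio from marginal standardisation of the logistic predictions, with delta-method or bootstrap confidence intervals;
- the logistic model as planned, with its result labelled an adjusted odds ratio and not set beside the unadjusted risk ratio as if on the same scale.

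The first two keep the risk ratio throughout and are preferable if the adjusted and unadjusted results are to be compared. In passing, reword the chi-squared sentence so that the risk ratio is between arms.

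The cost is a sentence or two in the analysis section. The data, covariates, sample size and primary test do not change. The article gives the trial as still recruiting, so on that status the change can be made before analysis.

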Current COVID-19 Treatment Guidelines recommend the use of dexamethasone in patients who require respiratory support [11–14]. Results from the Randomized Evaluation of COVid-19 thERapY (RECOVERY) trial demonstrated a reduction in 28-day mortality with 6 mg daily of dexamethasone for up to 10 days compared to standard of care in patients hospitalized with COVID-19 who were receiving either invasive mechanical ventilation or oxygen alone at randomization [15]. Patients without respiratory support needs did not seem to benefit from corticosteroid use. Similarly, in a prospective meta-analysis that pooled data from seven randomized clinical trials of critically ill patients with COVID-19, systemic corticosteroid administration was associated with lower 28-day all-cause mortality compared with usual care or placebo [16].

An increase in inflammatory biomarkers is known to correlate with progression to ARDS and mortality in COVID-19 patients. Available data provide evidence for the differentiation of severe and non-severe cases of COVID-19 based on inflammatory biomarkers including lactate dehydrogenase (LDH), C-reactive protein (CRP), and lymphocyte count [17, 18]. Elevated LDH increase mortality (OR, 4.22; 95% confidence interval [95% CI], 2.49–7.14) in patients with COVID-19 [19]. For each 100-unit increase in CRP levels, the odds of death increase twofold (OR, 2.01; 95% CI, 1.57–2.56) [20]. Finally, a lymphocyte count lower than 0.95 × 10^9^/L is associated with a risk of death compared to patients with lymphocyte counts greater than 0.95 × 10^9^/L (OR, 7.27; 95% CI, 1.10–48.25) [21].

As mentioned above, in the RECOVERY trial, dexamethasone did not reduce mortality in patients with SARS-CoV-2 pneumonia without the need for supplemental oxygen. Nevertheless, we postulate that the use of corticosteroids in COVID-19 pneumonia in its initial phases might have a different effect in patients with inflammatory biomarkers associated with disease progression. One-third of COVID-19 patients with mild symptoms at presentation will develop severe illness, particularly patients in whom biomarkers associated with COVID-19 disease progression are detected. Therefore, we conducted a study to evaluate whether the early administration of dexamethasone in hospitalized patients with COVID-19 pneumonia without additional oxygen requirements in whom biomarkers with a strong correlate with severe prognosis are detected, leads to a decrease in the development of ARDS and death.

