### Data collection and procedures study

All participating patients, regardless of the study arm into which they are randomized, will be monitored following general standard of care practices. Patients will be assessed once daily by local investigators.

Demographic data including age and sex assigned at birth, comorbidities, and the COVID-19 vaccination status from participants will be collected. Temperature, respiratory rate, cardiac frequency, peripheral capillary oxygen saturation (SpO2), respiratory support, partial pressure of arterial oxygen/fraction of inspired oxygen (PaO2/FiO2), quick Sequential Organs Failure Assessment (qSOFA) score, and the ordinal scale for clinical improvement of the World Health Organization will be monitored at least once daily. Biochemistry and haematological tests on days 1 and 7; and chest X-ray on days 1, 4, and 7; and discharge will be assessed (Table 2). Laboratory determinations will include haemoglobin, white blood cell, lymphocyte count, platelets count, glucose, blood urea nitrogen, serum creatinine, sodium, potassium, LDH, alkaline phosphatase, albumin, ALT, AST, total bilirubin, CRP, prothrombin time, D-dimer, ferritin level, interleukin-6, and procalcitonin. Patients will be followed up to 90 days after randomization.

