## Discussion

Up to one-third of patients with mild COVID-19 pneumonia develop ARDS [13]. In 25% of these patients, ARDS progresses rapidly, requiring urgent care in intermediate respiratory care or intensive care units [29]. Based on initial findings from the first reports from Wuhan, the use of systemic corticosteroids was not recommended in the treatment of patients with COVID-19 pneumonia, even in those at risk of ARDS [30]. However, the RECOVERY trial marked an inflexion point in the use of corticosteroids for the treatment of COVID-19 patients. The benefit was clear in patients with oxygen needs and in those treated more than 7 days after symptom onset, when inflammatory lung damage is likely to have been more common. No benefit in patients who did not require respiratory support was observed, according to the trial’s findings. Due to the elevated risk of progression to ARDS by approximately 30% of patients with COVID-19 pneumonia [2], identification of factors that allow for early identification and treatment of patients who will progress to ARDS is crucial. Inflammatory biomarkers such as LDH, CRP, and lymphocyte are independently associated with increased risk of severe disease [31], so tracking these markers might allow early identification or even prediction of ARDS Unfortunately, the RECOVERY trial did not collect laboratory biomarkers. Although early administration of corticosteroids could blunt the immune response in the initial stage of viral replication, the benefit of dexamethasone in this specific subpopulation of COVID-19 patients with hyperinflammation could be underestimated.

To test this hypothesis, we are conducting a trial to evaluate if the administration of dexamethasone in hospitalized patients with COVID-19 pneumonia who do not require supplementary oxygen and are at risk for severe disease leads to a decrease in the progression to ARDS and death. To our knowledge, this is the first prospective randomized controlled trial to evaluate the benefit of corticosteroids in this subgroup of patients with COVID-19.

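### The adjusted analysis of the primary outcome omits baseline LDH, CRP and lymphocyte count, which the protocol treats as independent predictors, selects patients on and measures on day 1

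*Protocol article*

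**What the plan says.** All references are to the Protocol article.

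- **Statistical analysis.** The test named for the primary endpoint is an unadjusted chi-squared comparison of the arms. A logistic regression then supplies adjusted risk ratios: "Adjustment will be performed for age, gender, and history of diabetes, hypertension, or obesity". Study site is added. The section justifies the list with a cited source that ranks these factors highest for mortality and progression. No biomarker appears.
- **Discussion.** "Inflammatory biomarkers such as LDH, CRP, and lymphocyte are independently associated with increased risk of severe disease". Justification of the study says much the same.
- **Background.** It gives an odds ratio of 4.22 for elevated LDH, and for CRP: "For each 100-unit increase in CRP levels, the odds of death increase twofold" (OR 2.01). Both figures concern death.
- **Inclusion criteria.** Entry needs at least two of three: LDH above 245 U/L, CRP above 100 mg/L, lymphocytes below 0.80 × 10^9/L.
- **Data collection and procedures study.** All three markers are in the laboratory panel taken on days 1 and 7.

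**The concern.** The trial rests on the idea that these three markers identify who will progress. The model meant to account for prognosis uses demographics, comorbidities and site, and leaves the markers out without comment.

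Selection narrows the spread of the markers but does not remove it. The cut-offs are one-sided, LDH and CRP have no upper limit, and the third marker may be normal. The Randomization section describes permuted blocks and mentions no stratification on the markers. A chance difference in baseline inflammation would therefore be corrected only as far as the listed covariates happen to track it. In an open-label trial, adding the markers after an imbalance has been seen would carry little weight, so the choice belongs in the plan now.

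**Working it through.** **1. The plan's own figure.** Inputs from Sample size and Randomization: "reduction of ARDS from 30% in the control group to 20% in the intervention group"; 80% power; two-sided alpha 0.05; 1:1 allocation. The stated result is 226 in total.

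n per arm = [1.960·√(2·0.25·0.75) + 0.842·√(0.30·0.70 + 0.20·0.80)]² / 0.10² = [1.200 + 0.512]² / 0.01 ≈ 293.2, so 294 per arm and 588 in total.

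The 226 does not reproduce. Power = Φ{(0.10·√n − 1.200)/0.608}, which is 41% at 113 per arm and 45% at 126 per arm. This is a separate problem. It matters here only because it sets the power level at which the covariates operate.

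**2. Events and parameters.** Expected events are 113·(0.30 + 0.20) = 56.5 and 126·0.50 = 63. Treatment plus five listed covariates is 6 parameters, or about 9.4 to 10.5 events each. With three markers it is 9 parameters, or about 6.3 to 7.0 each. Site terms come on top in both cases.

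**3. Chance imbalance.** For a baseline score in SD units, 95% of trials have a between-arm difference within 1.96·√(2/126) = 0.25 SD. Assume the score has log-odds SD s and is normally distributed, with marginal risks of 30% and 20%. Move each arm's mean by 0.125 SD in opposite directions and average the logistic risk over the score. The unadjusted risk ratio is 0.67 when balanced. At that limit it becomes:
- s = 0.6: about 0.74 or 0.60
- s = 1.0: about 0.78 or 0.57

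**4. Effect of adding the markers.** Simulation of 1,500 trials per setting at 126 per arm, with marginal risks held at 30% and 20%. Assumptions not in the document: five clinical covariates with joint log-odds SD 0.6; three markers with the joint log-odds SD shown; site not modelled. The variance ratio is that of the standardised log risk ratio, without markers divided by with markers.

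| Marker log-odds SD (assumed) | Power, listed covariates | Power, plus markers | Variance ratio | Mean SE of log odds ratio |
|---|---|---|---|---|
| 0 | 45.7% | 46.1% | 0.98 | 0.315 → 0.320 |
| 0.3 | 46.9% | 47.6% | 1.01 | 0.315 → 0.323 |
| 0.6 | 47.1% | 48.0% | 1.06 | 0.314 → 0.330 |
| 1.0 | 45.5% | 51.3% | 1.14 | 0.313 → 0.348 |
| 1.5 (extreme) | 45.5% | 57.3% | 1.34 | 0.311 → 0.375 |

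Monte Carlo error is √(0.45·0.55/1500) ≈ 1.3 points on each power. The chi-squared test stays at about 45%, since covariates do not enter it. The SE of the log odds ratio rises because a logistic model with more prognostic covariates estimates a different, conditional odds ratio. The gain therefore shows in power and in the standardised risk ratio, not in that SE.

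**The case against.** The strongest reply is that the plan already names a reasoned covariate set with a cited source, and that a different set is a matter of preference. Randomisation makes the unadjusted test valid, and its error rate already covers chance imbalance. Much of this stands. The omission is not an error of validity, and nothing in the document shows that the listed factors are poorly chosen. It does not explain why markers that the same document calls independent predictors are left out.

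Four stronger readings are tempting, and the document does not support them.

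- **That the primary analysis itself loses power.** The named primary test is unadjusted. The covariate list affects only the accompanying estimate.
- **That the quoted odds ratios show a large loss of precision.** They are for death, whereas the trial is powered on ARDS. The LDH contrast of elevated against not elevated is also largely used up by the entry rule. No figure gives the markers' strength for ARDS among enrolled patients, and it could be weak.
- **That the markers come free.** They need no new data, but three more parameters count with so few events.
- **That vaccination status should be added, or comorbidity terms swapped out.** The protocol says "the COVID-19 vaccination status from participants will be collected" but gives no prognostic evidence for it. Nothing in the document shows that the comorbidity terms are the weaker ones.

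**Conclusion.** The point holds as a modest improvement to the adjusted analysis. The stated covariate list fits badly with the trial's own rationale, and the missing variables are already collected.

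The size is uncertain. Assumed within-trial log-odds SDs of 0 to 1.0 give about nil to 14% in effective sample size, and 0 to about 6 points of power for the adjusted treatment term. Up to an SD of 0.6 the power gain is about one point or less, within simulation error. Power did not fall in any setting; the worst variance ratio, 0.98, occurs when the markers carry no information. These figures assume the Sample size event rates apply to the composite outcome, and they leave site terms out.

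No setting comes near 80% power. The shortfall of 226 stated against 588 recomputed is a much larger issue and is untouched by this change.

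**What to change.** In Statistical analysis, add baseline log-LDH, log-CRP and lymphocyte count to the pre-specified logistic model as continuous covariates. State that pre-treatment values are used, since the first dose and the first panel both fall on day 1. Keep the listed covariates and site. Report the adjusted result as a standardised (marginal) risk ratio, obtained by averaging the model's predicted risks over all patients under each arm. If the markers are left out on purpose, give the reason.

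The cost is a short change of text, about three extra parameters, and a standardisation step in the analysis. Making the adjusted estimate primary is a separate decision. Without it, the chi-squared result stays as it is.
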